# Safety and therapeutic effects of personalized transcranial direct current stimulation based on electrical field simulation for prolonged disorders of consciousness: study protocol for a multi-center, double-blind, randomized controlled trial

**DOI:** 10.3389/fneur.2023.1184998

**Published:** 2023-06-29

**Keywords:** non-invasive brain stimulation, DOC, consciousness, transcranial direct current stimulation, neuromodulation, clinical trial, minimal consciousness state, vegetative state

## Abstract

**Background:**

Disorders of consciousness (DOC) resulting from acquired brain injury (ABI) increase the mortality rate of patients, complicate rehabilitation, and increase the physical and economic burden that DOC imposes on patients and their families. Thus, treatment to promote early awakening from DOC is vital. Transcranial direct current stimulation (tDCS) has shown great potential for promoting neuro-electrochemical activity. However, previous tDCS studies did not consider structural damage or head and brain lesions, so the applicability of the results to all DOC patients was limited. In this study, to establish a patient-specific tDCS treatment plan considering the brain lesions of and damage sustained by DOC patients, we considered the electric field calculated by a the “finite electric” three-dimensional brain model based on magnetic resonance images. This protocol was developed to aid tDCS treatment of actual patients, and to verify its safety and effectiveness.

**Discussion:**

For patients with neurological disorders, tDCS has served as a painless, non-invasive, easily applied, and effective therapy for several decades, and there is some evidence that it can improve the level of consciousness of patients with DOC. However, variability in the effects on consciousness among subjects have been reported and personalized strategies are lacking. This protocol is for a randomized controlled trial designed to validate the effectiveness and safety of P-tDCS combined with typical rehabilitation for DOC.

**Clinical trial registration:**

https://cris.nih.go.kr, identifier KCT0007157.

## Introduction

Acquired brain injury can result in prolonged disorders of consciousness (DOC) including coma, “unresponsive wake syndrome” (UWS; also called vegetative state [*VS*]) (1) and a minimally conscious state (MCS) (2). Several studies have attempted to determine the effectiveness of brain stimulation techniques, such as deep brain stimulation (DBS) (3), transcranial magnetic stimulation (4), and transcranial direct stimulation (tDCS), for improving the level of consciousness of patients with DOC (5). In particular, tDCS therapy is emerging as a non-invasive treatment, with no side effects such as seizures (6).

tDCS is a form of cortical stimulation in which anode and cathode electrodes are attached to the scalp or forehead and continuous direct current is applied. Several studies have reported that anodal stimulation of the damaged cortical area in DOC patients improves the function of the stimulated area. The dorsolateral prefrontal cortex (DLPFC) is the most important target region to improve consciousness in DOC patients. One study showed that a single session of tDCS over the left DLPFC improved the level of consciousness in 43% of patients in an MCS (7) In a study of UWS and MCS patients, tDCS was used to activate the left DLPFC and restore consciousness, and all MCS patients showed immediate clinical improvement after the tDCS intervention. Patients who received a second tDCS treatment 3 months after the first showed additional clinical improvement and the emergence of consciousness (8). In another study, consciousness was restored in chronic MCS patients through repeated tDCS treatment, and a significant change in the Coma Recovery Scale-Revised (CRS-R) score was seen compared with a sham tDCS treatment. Moreover, recovery of consciousness was maintained for up to 1 week after the end of tDCS treatment (9). tDCS has also been applied in clinical settings, as it can easily be customized by varying the position, size, number, and current of electrodes without any major adverse events.

Several studies have attempted to improve the effectiveness of tDCS for patients with DOC. The retrospective study described above divided patients with DOC into groups that did and did not recover consciousness (9). In that study, left DLPFC tDCS correlated with less metabolic impairment in distant brain regions, as well as in regions presumably stimulated by tDCS. Studies have begun to explore why tDCS treatment is not effective in all patients; differences in the severity of the disability, location or size of the brain lesion, and structural characteristics of the brain around the lesion have all been implicated.

tDCS has emerged as a major research interest. However, studies have only been performed retrospectively; no actual patients have been recruited and personalized tDCS (P-tDCS) has not been performed. Precise modeling and simulation are often precluded by the patient’s surgical history, a pre-existing implant device, or a skull defect. Datta (10) performed a simulation study to test the effect of a pre-existing device on the tDCS-induced electrical field and reported no significant interference. We will apply P-tDCS to patients with DOC, with a focus on safety. The goal is to provide evidence that tDCS can be applied as a new treatment method other than medication or existing physical therapy for DOC patients who have been excluded from several previous studies, considering that it may not be safe to receive tDCS treatment due to skull defects or medical history. To achieve that goal, this study will consider the electric field values generated in the target area for consciousness recovery with a simulation-based P-tDCS method and perform a tDCS simulation. This clinical trial aims to develop P-tDCS programs to restore consciousness in DOC patients in a *VS*/UWS or MCS. Sham tDCS will serve as the control. Whether P-tDCS treatment based on brain magnetic resonance imaging (MRI)-optimized tDCS is safer and more effective than sham tDCS will be assessed.

## Materials and methods

### Trial design

A prospective, randomized placebo-controlled cross-over double-blind multicenter phase 2 feasibility study will be performed (Figure 1; Table 1). P-tDCS will be compared to sham tDCS in patients in a *VS*/UWS or MCS (8, 11). Typical rehabilitation will also be applied, such as physical or occupational therapy for 1–2 h per day (5 days per week). The therapies will be performed passively, i.e., not in a goal-oriented manner, due to the debilitating nature of DOC.

**Figure 1 fig1:**
[figure not shown]
The study protocol.

**Table 1 tab1:** Study design.

	Screening	Baseline	Period 1		Outcome	Wash-out period	Period 2		End of study
			Session 1	Session 2			Session 1	Session 2	
Visit	V1	V2	V3 ~ V6	V7 ~ V11	V11	2 weeks	V12 ~ V16	V17 ~ V21	V22
ENROLLMENT									
Informed consent	**V**								
Eligibility screen	**V**	**V**							
Randomized allocation		**V**							
Taking a clinical photo	**V**								
MRI-based simulation and planning for tDCS		**V**							
INTERVENTIONS									
Personalized tDCS Sham-tDCS		**V**	**V**	**V**			**V**	**V**	
ASSESSMENTS									
Outcome variables		**V**							
Vital signs	**V**	**V**	**V**	**V**	**V**	**V**	**V**	**V**	**V**
Physical examination	**V**	**V**							
K-CRS-R		**V**			**V**				**V**
EEG		**V**							**V**
NCS-R		**V**	**V**	**V**	**V**	**V**	**V**	**V**	**V**
MRI, fMRI, and PET scan		**V**							**V**
Other variables Adverse events		**V**	**V**	**V**		**V**	**V**	**V**	**V**

### Participants involvement and ethics approval

This protocol was approved by the Korean Ministry of Food and Drug Safety and complied with the ethical standards of the Declaration of Helsinki. The final protocol was approved by the Ethics Review Boards of St. Vincent’s Hospital and Bucheon St. Mary’s Hospital (Catholic University of Korea; approval number: XC21DDDS0158), as well as the National Traffic Injury Rehabilitation Hospital (approval number: NTRH-21027). Written informed consent will be obtained from each participant’s legal guardian.

### Recruitment

Participants will be screened and recruited from three hospital in the Republic of Korea: St. Vincent’s Hospital, Bucheon St. Mary’s Hospital, and the National Traffic Injury Rehabilitation Hospital.

### Inclusion and exclusion criteria

The inclusion criteria that will be applied in the study are as follows: aged 19–80 years; acquired brain injury patients diagnosed with *VS*/UWS or MCS based on the results of the Korean version of the Coma Recovery Scale-Revised (K-CRS-R), administered at least twice within 1 week (12); stable, without any change in medication or other treatments for underlying diseases at least 1 week before the screening date, and scheduled to receive medication or treatment during the study period.

The exclusion criteria that will be applied are as follows: alcohol and drug induced change of consciousness; brain tumor; degenerative disease such as Parkinson’s syndrome; unable to undergo tDCS due to scalp disease; a pre-existing implant device in the brain or skull with a location corresponding to the tDCS electrode attachment sites; use of a stimulation device similar to the medical devices used in this study within the last 1 year or experience participating in related clinical trials; clinically unstable vital signs; unsuitable for tDCS due to surgery that caused structural changes in the brain (e.g., lobectomy or extensive cranial defects), and a medical condition that may affect consciousness.

### Enrollment and randomization

Participants will be assigned a random number at baseline and randomized to either Group A or Group B. As this trial uses a cross-over design, the only difference between the two groups is the order of the intervention [Group A: P-tDCS (period 1), washout period (> 2 weeks), and sham tDCS (period 2); Group B: sham tDCS (period 1), washout period, P-tDCS (period 2)].

All participants will be randomly assigned to the groups at a 1:1 ratio according to the order of registration by the investigator. The statistician for this clinical trial will use the latest version of SAS statistical software (SAS Institute, Cary, NC, USA) to issue random numbers. A stratified block randomization method will be used with a predefined block size; institution will be a stratification factor. Envelopes containing the study numbers will be provided to the “investigational device manager” (IDM) before the participants are registered.

To maintain blinding of the IDM, an unblinded investigator will be assigned to each institution, and will provide the participants with devices according to their group assignments. The unblinded investigators will not participate further in the study.

This parallel randomized controlled trial uses a cross-over design given the clinical needs of the DOC patients. There is no gold standard treatment for DOC, although tDCS may be useful. However, use of tDCS is prohibited in Korea, except in clinical trials, and the treatment options for DOC patients are limited. Benefits of tDCS have been reported in some cases of DOC (13). Because sham group patients would not receive any of the benefits of tDCS due to the parallel study design, a cross-over design is used so that all participants will have the same opportunity to receive tDCS.

### tDCS treatment, simulation, and blinding

After being assigned a study number, the IDM will take photographs with a digital camera to determine the condition of the participant’s scalp and forehead; redness or burns caused by the medical device will be checked, and changes will be recorded. This process will help minimize side effects. After unblinding, the IDM will select electrode positions based on simulations performed using Neurophet tES Lab (ver. 3.0; Neurophet, Seoul, South Korea); the electrodes will then be attached. P-tDCS will be performed using Neurophet tES Lab; three-dimensional (3D) T1 MRI images of the participants will be imported into the software, brain tissue will be segmented, and a mesh will be generated. Brain tissue will be divided into eight layers: skin, skull, cerebral and cerebellar white matter, gray matter, cerebrospinal fluid, and affected tissue (14). A 3D brain model will be created based on the segmentation and mesh. Points in front of both ears, the nasion, and the inion will serve as landmarks in the brain model, which will be optimized using the software. To optimize the P-tDCS, 5 × 5 cm^2^ electrodes will be deployed in a representative area of the left DLPFC, which is the target area for stimulation to recover consciousness. The simulation parameters for determining the optimal electrode position include the initial positions of the anode electrode (F3) and cathode electrode (Fp2), which are based on the international 10–20 electroencephalography (EEG) system. The simulation will begin after inputting these parameters. After completing the simulation, the IDM will check the results and positions of the electrodes, and prepare for the actual tDCS intervention.

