#### tDCS device

The tDCS treatment will be applied using a battery-driven, portable tDCS device (Neurophet innk; Neurophet) and two sponge-coated 5 × 5 cm^2^ electrodes. The stimulation parameters will be set using the bundled software. The parameters in Group A will be as follows: tDCS mode, current intensity of 2 mA, and simulation time of 30 min. In Group B (sham tDCS), the sham mode of the software will be used; the stimulation time will be the same as in Group A, while the current will be increased to 2 mA over the first 30 s and then decreased to 0 mA over the next 30 s (15). The current will then be maintained at 0 mA for the next 28 min, increased to 2 mA over 30 s, and finally decreased to 0 mA over the next 30 s.

The tDCS device can check impedance in real time. If the impedance is >13 kOhm, the stimulation will be stopped and the IDM will check the condition of the patient’s skin to prevent adverse events.

Each tDCS intervention will be performed 10 times over 2 weeks. Then, the other tDCS intervention will be performed depending on the group assignment. Any rehabilitation programs in which the participants are enrolled can be continued during the study. The electrode locations will be the same in the sham tDCS and P-tDCS groups.

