## Discussion

This randomized, multicenter clinical trial will investigate the immediate and delayed effects of tDCS on the level of consciousness and EEG activity of patients with prolonged DOC. Although previous studies have reported improvements in the level of consciousness after applying tDCS to the F3 region of *VS*/UWS and MCS patients, no clear conclusions were drawn due to methodological limitations and differences in effects among studies and individuals. In addition, most previous studies excluded patients with a history of brain surgery. This trial is being performed to overcome these limitations; it is expected to have relatively high internal validity because participants will be randomly assigned to groups, randomization concealment will be implemented, and raters, participants, and the IDM will be blinded.

Although the neurophysiological and electrophysiological effects of tDCS have been confirmed, and safety has been demonstrated (19, 26), its clinical utility remains to be verified. This clinical trial will aim to determine the effects of P-tDCS treatment in UWS and MCS patients, and the role of simulated electric fields. If tDCS can be proven to provide clinical benefits, it could serve as an important treatment for patients with cognitive impairments.

In closing, this trial has been designed to validate the safety and effectiveness of P-tDCS developed based on each participant’s T1-weighted MRI scans and the results of simulations. The aim is to determine whether P-tDCS is a viable therapy for DOC patients with a surgical history, skull defects, or pre-existing implantable device. Recently developed simulation technologies and Neurophet tES LAB software will be used to this end; in particular, the latter will be used for segmentation and 3D brain modeling.

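### The investigational device manager is declared blinded in two places but acts after unblinding in a third, so that person's skin-safety observations are not assuredly blind

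*Protocol article*

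**What the plan says.** Three places in the Protocol article speak to whether the IDM knows the treatment.

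- Enrollment and randomization: "To maintain blinding of the IDM, an unblinded investigator will be assigned to each institution". That investigator hands out devices according to group, and then: "The unblinded investigators will not participate further in the study".
- Discussion, as a ground for high internal validity: "randomization concealment will be implemented, and raters, participants, and the IDM will be blinded".
- tDCS treatment, simulation, and blinding: "After unblinding, the IDM will select electrode positions based on simulations performed using Neurophet tES Lab". The electrodes are attached after that step.

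Three further statements bear on the point. On the envelopes, Enrollment and randomization says: "Envelopes containing the study numbers will be provided to the" IDM before participants are registered. On placement, the section tDCS device says: "The electrode locations will be the same in the sham tDCS and P-tDCS groups". On the control condition, the same section says that "the sham mode of the software will be used", without naming who sets it.

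The IDM also has observational duties. The IDM photographs the scalp and forehead, and the same procedure includes checking for redness or burns and recording changes. The IDM also inspects the skin when impedance exceeds 13 kOhm and stimulation is stopped.

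**The concern.** The trial is labelled double-blind and offers the IDM's blinding as one reason to trust its results. A site that followed the treatment section literally would unblind the IDM before electrode positions are chosen, and the claimed property would be lost at the start of each patient's treatment.

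The practical consequence lies in safety. Whether P-tDCS is safer than sham is part of the stated aim, and deciding whether skin looks reddened or changed involves judgement. If the person looking knows the treatment, the comparison of skin findings between active and sham periods is open to that knowledge. In this two-period cross-over, knowing the treatment in one period also gives the other, so one unblinding covers both of a patient's periods.

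**Working it through.** No figure in the plan depends on this point, so the check is a comparison of text.

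1. **Status of the IDM.** Enrollment and randomization: blinded, with a role created to protect this. Discussion: blinded. tDCS treatment, simulation, and blinding: acts after an unblinding. The last sentence does not say who is unblinded or to what. On its ordinary reading, the allocation is known when the IDM chooses positions, which conflicts with the other two.

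2. **Does the step need the allocation?** The P-tDCS section derives the anode position from the MRI-based head model and the simulated field in the left DLPFC. Locations are the same in both conditions. Neither statement gives a reason to know the sequence first. Table 1 puts randomized allocation and MRI-based planning at the same baseline visit (V2) without ordering them, so planning without the allocation fits the existing schedule.

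3. **Which observations are exposed?** Table 1 marks the clinical photograph at screening (V1) only, before allocation at V2, although the text places it after a study number is assigned. On the Table 1 timing, that photograph precedes any unblinding. The exposure is then in the later checks for change and the skin inspections at high impedance. The impedance check is explicitly the IDM's. The redness and burns check is written in the passive within the IDM's procedure, so attributing it to the IDM is the natural reading but not an explicit one.

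4. **Who could learn the mode?** Sham is a software mode and every patient changes condition at cross-over. The unblinded investigator takes no further part after providing devices. The article names nobody who sets the mode in either period. A device preset for each period would be consistent with the text, and so would an IDM who sees the mode. The article does not settle which applies.

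5. **Extent.** The IDM's procedure applies to each of the 24 planned patients. Each receives 10 sessions per intervention, so 2 × 10 = 20 per patient and 24 × 20 = 480 in all. This counts planned sessions. The article does not say that the IDM runs or attends each one.

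**The case against.** The strongest reply is that one short phrase in a condensed article is being set against two clear statements of a blinded IDM, and that the phrase may be a drafting slip. The intended design probably is a blinded IDM. But the phrase stands in current text, in the section that describes blinding, and tells the IDM when to act. It needs correcting even if it is a slip.

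The reply is right against several stronger readings that a reader might infer.

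- **Concealment fails because the IDM holds the envelopes.** The envelopes are said to contain study numbers. Nothing says they show the group, and use of the group assignment is given to the unblinded investigator. One could add that someone who knew past allocations and the block size could deduce some future ones. For 1:1 permuted blocks of size 2k the share is 1/(k+1): 50% for blocks of 2, 33% for blocks of 4, 25% for blocks of 6. That requires an unblinded IDM, a known block size (not given) and influence on enrolment. The article states neither of the last two.
- **The double blind as a whole fails and K-CRS-R is biased.** Raters and participants are separately stated to be blinded, and the treatment section does not contradict this. The IDM is not named as a rater of K-CRS-R or NCS-R. Daily contact between the IDM and raters or guardians is not described.
- **Electrode placement is biased.** A location shared by both conditions, in patients who each receive both, gives no evident route to a treatment difference.

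Skin reactions are also not listed by name among the safety endpoints, which are NCS-R, vital signs and concomitant drugs. They would enter through adverse events, which the abstract says are recorded at each session.

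**Conclusion.** The contradiction is real and should be resolved. The article says the IDM is blinded and also has the IDM act after unblinding, at a step for which no need of the allocation is apparent. As written, the IDM's blinding is not assured, and neither is the blinding of the skin-safety observations in the IDM's procedure. The size of any bias cannot be computed from the article.

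The conclusion assumes that unblinding refers to treatment allocation and that the IDM carries out the skin checks described in the IDM's procedure. It does not extend to allocation concealment, to the raters or participants, or to the primary outcome, because the text does not show a failure in any of these.

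**What to change.** Reconcile Enrollment and randomization, tDCS treatment, simulation, and blinding, and the Discussion, as follows.

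1. In the treatment section, have the IDM complete and lock segmentation, simulation and electrode-position selection without knowing the allocation. Remove the reference to unblinding, or explain it if it means something else. State that the IDM stays blinded throughout.
2. State that the study-number envelopes given to the IDM do not reveal the group.
3. Name who sets sham or active mode in each period, including after cross-over. If this is the unblinded investigator, amend the sentence that ends that person's involvement so that it permits this one task and excludes any outcome or safety assessment. Without that amendment the change would create a new contradiction.

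The cost is a few sentences, an explicit task order within the baseline visit, and, if the unblinded investigator sets the mode, a small continuing task for a role already planned at each site. No extra patients, visits or assessments are needed.
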